### Outcomes

The primary outcome is the rate of 30-day, nonelective readmissions to any of the 30 hospitals affiliated with the sponsoring healthcare system. We followed the definition for nonelective readmissions as set out by the Centers for Medicare and Medicaid Services (CMS); however, we included both inpatient and observation classifications to create an outcome that is more patient-centered (Fig. 3). To allow for nondifferential outcome assessment, we use only data that are collected and available as part of routine care. Secondary outcomes include the 30-day nonelective readmission rates separated by inpatient and observation classifications (Fig. 3), 30-day emergency department use, 30-day acute care use composite (primary outcome of readmission plus emergency department use), 60- and 90-day readmission rates (using primary outcome definition of readmission), and length of stay on index and readmission visit. Additionally, in cost analysis, we will compare the total patient charges at 30, 60, and 90 days across groups with modeling of cost inclusive of estimated readmission penalties. To provide an understanding of implementation factors, RE-AIM measures are reported to the care team through monthly automated reports (Table 2) [18]. Because this evaluation is also designed to inform a quality improvement project, we expect that the clinical team may use the RE-AIM measures to adapt the transition services program during the course of the evaluation. Any substantial changes in process, procedures, or services will be documented and incorporated into the outcome analyses.

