## Abstract

**Background:**

Hospital readmissions remain highly prevalent despite being the target of policies and financial penalties. Evidence comparing the effectiveness and costs of interventions to reduce readmissions is lacking, leaving healthcare systems with little guidance on how to improve quality and avoid costly penalties. Effective interventions likely need to bridge inpatient and outpatient settings, incorporate information technology, and use dedicated providers. Such complex innovations will require rigorous evaluation. The framework of quality improvement research provides an approach that both improves care locally and contributes to closing the current knowledge gaps for readmissions. In this trial, we will study a comprehensive intervention that incorporates these recommendations into an integrated practice unit, called *transition services*, with an aim of reducing 30-day readmission rates.

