## Methods/design

### Overview

AIRTIGHT is a nonblinded, pragmatic, controlled trial with two parallel groups in which we are evaluating the effect of referral to a provider-led IPU, inclusive of comprehensive multidisciplinary care and virtual visits, on 30-day readmission rates for high-risk hospitalized patients (Fig. 1). The primary outcome of 30-day, all-cause, any-site readmission will be retrieved electronically from administrative medical record data. Secondary outcomes will all be retrieved in a similar fashion and include 30-day single-site readmission, emergency department use, 60- and 90-day readmissions, length of stay on index admission and readmission, and cost. To provide an understanding of implementation factors, the RE-AIM (Reach, Effectiveness, Adoption, Implementation, Maintenance) framework is incorporated into the study design [18]. The trial is pragmatic across all nine PRECIS-2 domains (Fig. 2). In keeping with this pragmatic framework, the research team has no contact with participants during any aspect of the evaluation. Randomization, patient tracking, and outcomes are all conducted electronically. The AIRTIGHT trial is registered with ClinicalTrials.gov (NCT02763202).

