### Sample size

This study is designed to detect a 30% relative reduction in the readmission rate, with the usual care group assumed to have a 20% readmission rate in 30 days. A relative reduction of 30% was based on estimates from randomized controlled trials looking at bundled transition interventions and intensive home interventions [9, 20–22]. We will have 80% power to detect this reduction (transition services group rate reduced to 14%) with a total sample size of 1230 (α = 0.05) using a chi-square test for independence. Assuming 10% of those assigned to transition services will not participate, we must increase our sample size to 1520 (*n* = 760 per arm) to account for the anticipated decrease in the effect size. At the time of protocol design, available historical data included only the more narrow CMS definition of single-site readmissions (secondary outcome). Thus, the assumptions used in the power analysis are reflective of more conservative estimates than would be expected for the primary outcome measure’s expanded definition for readmission, which includes inpatient and observation stays between any of the acute care hospitals.

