### Analysis

All analyses will follow intention-to-treat principle such that patients will be analyzed on the basis of the group to which they were initially randomized, but after reapplication of inclusion and exclusion criteria at the time of hospital discharge (Fig. 1, “Eligible at discharge” bubble). Baseline comparisons of the two groups will be made using univariate analyses such as the *t* test and chi-square test. The primary outcome, readmission in 30 days, will be compared between the two groups of patients who are eligible at discharge, using logistic regression. Results will be presented with ORs and 95% CIs. In addition to the intention-to-treat analysis, we will perform a per-protocol analysis to evaluate the patients who are eligible at discharge and participate in the transition services program compared with usual care patients who are eligible at discharge. For all outcomes, we assume that if there are no visits in the electronic medical record, the value for having a visit is null; therefore, there will be no missing data for the primary or secondary outcome measures.

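### Length of stay on the readmission visit exists only for readmitted patients, so comparing it between arms has no causal reading; hospital days over all analysed patients would

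*Protocol article*

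**What the plan says.** The Outcomes section of the protocol article ends its list of secondary outcomes with "length of stay on index and readmission visit". The Overview names the same item as "length of stay on index admission and readmission". Under Outcomes and the Fig. 3 caption, a readmission may be an inpatient or an observation stay.

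The Abstract presents the program "with an aim of reducing 30-day readmission rates", and 30-day readmission is the primary outcome. The Sample size section sets the target: "This study is designed to detect a 30% relative reduction in the readmission rate". The planning rate for controls is given separately, "with the usual care group assumed to have a 20% readmission rate in 30 days", and the other arm is described as "transition services group rate reduced to 14" percent.

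The Analysis section puts every analysis on an intention-to-treat footing among patients still eligible at discharge, and names logistic regression for the primary outcome. For a patient with no recorded visit it sets the visit indicator to null, and it draws this conclusion: "therefore, there will be no missing data for the primary or secondary outcome measures". It assigns no length of stay to a patient who was not readmitted. No listed outcome counts hospital days over all analysed patients. The nearest whole-group measure is total charges at 30, 60 and 90 days.

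**The concern.** A patient has a readmission length of stay only after being readmitted, and readmission is the event the program tries to prevent. The outcome is therefore defined on a subset formed after randomisation, and its membership depends on assignment. If the program works, the readmitted patients in the two arms differ in kind as well as in number. A difference in their mean stay then mixes two things: any effect on how long a stay lasts, and a change in which stays happen at all.

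What is at stake is how hospital use is interpreted. A health system reading this outcome could conclude that the program lengthens or shortens readmissions when it has only changed which patients come back.

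**Working it through.** **Step 1. Design rates.** The rates used below come from the Sample size section: 20% against 14%, 80% power, α = 0.05 (two-sided assumed), chi-square test. Pooled-variance formula per arm:

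n = [1.960·√(2·0.17·0.83) + 0.842·√(0.20·0.80 + 0.14·0.86)]² / 0.06², which is just over 614 and rounds up to 615. The total is 1230, as stated.

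With 10% non-participation the intervention rate is 0.9 × 14% + 0.1 × 20% = 14.6%. The same formula then gives 770 per arm, or 1540 in total, close to the stated 1520; power at 760 per arm is 79.5%. None of these figures is in dispute.

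**Step 2. Who has a value.** Assume 760 analysed patients per arm.

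- Control: 760 × 0.20 = 152.
- Intervention: 760 × 0.14 = 106, or 760 × 0.146 = 111.
- Without a value: 80% of control and 85.4 to 86% of intervention patients.

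**Step 3. What selection alone can do.** The article gives no lengths of stay, so these are assumptions. Let readmissions be short (S days) or long (L days), with a share m of control readmissions short. Let p be the intervention readmission rate and f the fraction of prevented readmissions that are short. Assume no effect on the length of any stay that still occurs.

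- Control mean among the readmitted = mS + (1 − m)L.
- Remaining short stays: s = 0.20m − (0.20 − p)f.
- Remaining long stays: l = 0.20(1 − m) − (0.20 − p)(1 − f).
- Intervention mean among the readmitted = (sS + lL)/(s + l).
- Intervention days per patient = sS + lL.

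Worked case with S = 2, L = 7, m = 0.5, p = 0.14, per 100 patients. Control has 10 short and 10 long stays: 90 days, mean 90/20 = 4.50.

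| Readmissions prevented | Remaining (short, long) | Mean among readmitted | Difference | Days per 100 (control 90) |
|---|---|---|---|---|
| 6 short | 4, 10 | 78/14 = 5.57 | +1.07 | 78 |
| 3 short, 3 long | 7, 7 | 63/14 = 4.50 | 0 | 63 |
| 6 long | 10, 4 | 48/14 = 3.43 | −1.07 | 48 |

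**Step 4. Range.** I varied (S, L) over (2, 7), (3, 6) and (3, 8), m over 0.5 and 0.6, and p over 0.14 and 0.146:

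- only short stays prevented: +0.44 to +1.07 days;
- proportional prevention: 0;
- only long stays prevented: −0.55 to −1.29 days.

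Days per patient fall in every case. That follows from the set-up, since readmissions are removed and none is lengthened. The mean among the readmitted nevertheless moves in either direction or not at all.

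**Step 5. A second illustration.** Take 14 stays of 6 days and 6 of 3 days per 100 controls, with the program removing the 6 short ones.

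- Mean stay: (84 + 18)/20 = 5.1 days becomes 84/14 = 6.0 days, a rise of 0.9/5.1 = 18%.
- Days per 100 patients: 102 becomes 84, a fall of 18/102 = 18%.

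**The case against.** The strongest reply is that the article only names this outcome. It gives no analysis set, summary measure or test for it, and such detail is commonly left to the full protocol or analysis plan. The result may be meant as descriptive. The no-visit rule might also be intended to give zero days to patients who are not readmitted. Readers will see the readmission rates, the acute care composite and total charges beside it, and none of those is restricted to readmitted patients.

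Part of this stands. The intended analysis may be harmless, and total charges partly cover the burden. But the outcome as named has a value only for the readmitted, and the no-visit rule settles only whether a visit occurred. If zeros were intended, the measure would be hospital days per patient, a different outcome that should be named as such.

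Three stronger readings are tempting, and the document does not support them.

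- A reader might infer that the comparison will make a working program look worse. The direction depends on which readmissions are prevented, and the 18% illustration needs every prevented stay to be a short one.
- A reader might infer a flat contradiction with the statement that nothing is missing. A stay that never occurred is better called not applicable than missing, so that conflict is weak.
- A reader might infer that the outcome distorts the cost results. The Outcomes section bases cost on total charges and estimated penalties, and nothing there feeds readmission length of stay into it.

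**Conclusion.** The point holds as a limit on what this outcome can show. An arm comparison of length of stay on the readmission visit conditions on the event the program is designed to change, and it has no causal reading even if the plan is followed exactly. Under the assumed stays, selection alone shifts the difference by anything from −1.29 to +1.07 days. The size and sign in this trial cannot be known from the article; what is certain is that the subset depends on assignment if the program has any effect on readmission.

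The reach is narrow: one half of one secondary outcome. Index length of stay does not depend on readmission. The primary analysis, sample size and charge comparison are unaffected. It is worth correcting because a better measure can be built from data already collected.

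**What to change.** By a dated amendment, made before outcome analysis:

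- Add total inpatient plus observation days after index discharge within 30 days (and 60 and 90 if wanted) for every patient eligible at discharge, counting zero if there are none. Compare the arms by the difference in mean days with a bootstrap interval.
- Report recorded deaths by arm beside it, because early death also yields few hospital days.
- Keep length of stay among the readmitted as descriptive only, shown with the number readmitted per arm.
- State in the Analysis section that length of stay on the readmission visit is not applicable to patients without a readmission.

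The Data collection section already has hospital encounter data drawn from the enterprise data warehouse, so no new data source should be needed. The cost is a small documented change to one secondary outcome. The Trial status section says the trial is enrolling, so this should be recorded as an outcome amendment and not treated as a wording edit.

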**Fig. 3 Fig3:**
[figure not shown]
Patient-centered readmission. *The primary outcome is the difference in 30-day readmission rates between facilities. A readmission visit can be either an inpatient or an observation visit. Secondary outcomes include the difference in 30-day readmission rates between facilities. In one analysis, a readmission visit can only be an inpatient visit, and in another analysis a readmission visit can only be an observation visit

**Table 2 Tab2:** RE-AIM (Reach, Effectiveness, Adoption, Implementation, Maintenance) framework

RE-AIM measure	Metrics
Reach: How do I reach the target population?	• Capture rate: proportion of patients interested in program participation out of those who are referred and appropriate at the time of discharge • Show rate: proportion of patients who have a visit with the program out of those who are referred and appropriate at the time of discharge
Effectiveness: How do I know my intervention is effective?	• Absolute and observed/expected 30-day readmission rates as defined by CMS and reported as a routine quality metric by the healthcare system
Adoption: How do I develop organization support to deliver my intervention?	• Qualitative evaluation of program and participating primary care providers, which will be reported separately
Implementation: How do I ensure the intervention is delivered properly?	• Absolute and mean visit counts and visit type by month for the clinic as a whole and per patient • Proportion of patients with a medicine reconciliation and provider visit in 72 h out of all participating patients
Maintenance: How do I incorporate the intervention so it is delivered over the long term?	• Institutional level: Reach, Effectiveness, and Implementation measures for 3 months after conclusion of trial • Patient level: 90-day readmission and composite ED and hospitalization rates • Patient level: Qualitative substudy evaluating effect of intervention more than 60 days after last contact

*CMS* Centers for Medicare and Medicaid Services, *ED* Emergency department

### Sample size

This study is designed to detect a 30% relative reduction in the readmission rate, with the usual care group assumed to have a 20% readmission rate in 30 days. A relative reduction of 30% was based on estimates from randomized controlled trials looking at bundled transition interventions and intensive home interventions [9, 20–22]. We will have 80% power to detect this reduction (transition services group rate reduced to 14%) with a total sample size of 1230 (α = 0.05) using a chi-square test for independence. Assuming 10% of those assigned to transition services will not participate, we must increase our sample size to 1520 (*n* = 760 per arm) to account for the anticipated decrease in the effect size. At the time of protocol design, available historical data included only the more narrow CMS definition of single-site readmissions (secondary outcome). Thus, the assumptions used in the power analysis are reflective of more conservative estimates than would be expected for the primary outcome measure’s expanded definition for readmission, which includes inpatient and observation stays between any of the acute care hospitals.

### Data collection

Each weekday morning, a list of eligible patients in both arms of the study is generated and stored in an SAS dataset. Patients randomized to referral to the transition services program have their information exported to an Excel file (Microsoft, Redmond, WA, USA) for use by the nurse patient navigator. It is within this file that the enrollment status is tracked by the nurse patient navigator. A patient’s choice to decline services through the transition services program is also tracked within this file. The day following list generation, enrollment status is incorporated into the SAS dataset.

Patient data such as demographics and information associated with their hospital encounters, emergency department encounters, and charges will be pulled from tables within the healthcare system’s enterprise data warehouse. Dashboards displaying patient demographics, appointment descriptions (i.e., arrived, no show, canceled visit), enrollment rates, and no-show rates are presented to the clinical teams in Tableau files [23].

### Analysis

All analyses will follow intention-to-treat principle such that patients will be analyzed on the basis of the group to which they were initially randomized, but after reapplication of inclusion and exclusion criteria at the time of hospital discharge (Fig. 1, “Eligible at discharge” bubble). Baseline comparisons of the two groups will be made using univariate analyses such as the *t* test and chi-square test. The primary outcome, readmission in 30 days, will be compared between the two groups of patients who are eligible at discharge, using logistic regression. Results will be presented with ORs and 95% CIs. In addition to the intention-to-treat analysis, we will perform a per-protocol analysis to evaluate the patients who are eligible at discharge and participate in the transition services program compared with usual care patients who are eligible at discharge. For all outcomes, we assume that if there are no visits in the electronic medical record, the value for having a visit is null; therefore, there will be no missing data for the primary or secondary outcome measures.

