**Methods/design:**

We describe a nonblinded, pragmatic, controlled trial with two parallel groups comprising an evaluation of the effect of referral to a provider-led integrated practice unit, inclusive of comprehensive multidisciplinary care, dedicated paramedicine providers, and virtual visits, on 30-day readmission rates for high-risk hospitalized patients. An automated risk-scoring system will randomly generate referrals to either transition services or usual care for 1520 hospitalized patients who score as high-risk for readmission. Transition services will then engage with patients in the hospital setting using a patient navigator and provide bridging outpatient services for the 30 days following discharge. All outcome data are retrieved electronically from administrative medical records. After reapplication of inclusion and exclusion criteria at the time of hospital discharge, analyses will follow the intention-to-treat principle such that patients will be analyzed on the basis of the referral group to which they were initially randomized.

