### Eligibility

Patients are eligible for referral if they are over the age of 18 years, are seen by a hospitalist, and have been categorized as an inpatient and as high-risk for readmission, defined as a risk score probability during the first 72 h of admission that is associated with a readmission rate greater than 20%. Patients are excluded if they have a primary residence more than 150 miles from the hospital; are admitted from or discharged to locations such as hospice, skilled nursing facility (SNF), or jail; leave the hospital against medical advice; have an acute psychiatric illness; have been referred as part of the AIRTIGHT evaluation in the previous 90 days; have attended a similar heart failure transitions clinic at discharge; or are being actively care managed for a cancer diagnosis or sickle cell disease. These latter groups have existing, robust care management services in place. Transition services was specifically designed to support the unique needs of patients being discharged to home; consequently, SNF patients were excluded, despite this being a group at high risk for readmission. Also, because the intervention is designed to begin during a patient’s hospital stay, the initial referrals occur early in the course of the hospitalization. However, because we expect changes in some patients’ criteria during the ensuing hospitalization course, the inclusion and exclusion criteria are applied again at discharge (Fig. 1, “Eligible at discharge” bubble).

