### Randomization and blinding

A referral list is generated each weekday morning by randomly selecting eligible patients during their initial 72 h of admission. A six-person block randomization scheme was used so that, at any point, there are three patients assigned to usual care and three patients assigned to the transition services program. SAS software (SAS Institute, Cary, NC, USA) was used to create this 1:1 allocation, with future allocations concealed from the clinical team [19]. The total referrals are constrained to no more than 30 patients per day, but the total may be adjusted downward on the basis of daily estimates of the transition services’ capacity. Given the nature of the intervention, it is not possible to blind patients or clinicians. For the interim and final outcome analyses, a study statistician and Data and Safety Monitoring Board (DSMB) are not blinded to treatment assignment.

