### Trial intervention and control

Control patients will receive usual care. Standard discharge care at both hospitals includes recommendations for follow-up appointments with a patient’s primary care physician, discharge summaries sent to primary care physicians, the arrangement of home health services based on each patient’s needs, and other outreach interventions such as follow-up care management phone calls.

In addition to usual care, patients referred to the intervention group are contacted during their hospital stay by a registered nurse patient navigator, invited to participate in the transition services program, and then followed for the remainder of their hospital stay. For 30 days following discharge, patients have access to the transition services program, which, in addition to a free-standing clinic, includes the following: (a) as-needed access to transition-dedicated internal medicine, pharmacist, paramedicine, behavioral health, and care management providers; (b) hospital follow-up evaluation with a medical provider, either virtually in the patient’s home facilitated by a paramedicine provider or in the transition clinic; (c) medication reconciliation by a pharmacist; (d) at least weekly contact with the care management team; (e) 24/7 phone support, 24/7 paramedicine visit availability, and same-day clinic scheduling; and (f) coordinated transition to the next appropriate care location after 30 days (Table 1). The intensity of the care provided is not prescribed but rather dictated by the care team and patient. At a minimum to qualify as having participated, patients will have an in-person or virtual visit with the transition services medical provider. Patients or their insurance providers are charged only for services that are billable under usual care, whereas all other services are provided by the healthcare system as part of care management.

**Table 1 Tab1:** Transition services program intervention components

Transition services components	Transition recommendations [10] and drivers of readmissions addressed
Referral to transition services program and introduction by patient navigator while patient is still hospitalized	• Dedicated transition personnel • Spanning inpatient and outpatient • Engagement • Discharge plan confusion

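### The primary analysis is called intention-to-treat but drops patients by eligibility re-checked at discharge, after an unblinded in-hospital intervention has begun, so selection could bias the odds ratio

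*Protocol article*

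**What the plan says.** The order of events, from the protocol article:

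- **Randomization** (Randomization and blinding): the weekday referral list is made by "randomly selecting eligible patients during their initial 72 h of admission". The same section says that patients and clinicians cannot be blinded.
- **Start of the intervention** (Trial intervention and control): patients referred to the program "are contacted during their hospital stay by a registered nurse patient navigator", are invited to take part, and are followed for the rest of the stay.
- **Second eligibility check** (Eligibility): "the inclusion and exclusion criteria are applied again at discharge". The reasons given are that referral has to happen early, that some patients' criteria are expected to change during the stay, and that the program was built for people going home.
- **Criteria on the list** (Eligibility): some are known at referral. Others are settled during or at the end of the stay: discharge to hospice, skilled nursing facility (SNF) or jail, and leaving against medical advice. One is worded "have attended a similar heart failure transitions clinic at discharge".
- **Primary analysis** (Analysis): "All analyses will follow intention-to-treat principle such that patients will be analyzed on the basis of the group to which they were initially randomized". The sentence goes on to restrict this with the words "but after reapplication of inclusion and exclusion criteria at the time of hospital discharge". The 30-day readmission outcome "will be compared between the two groups of patients who are eligible at discharge, using logistic regression". The abstract says the same: "After reapplication of inclusion and exclusion criteria at the time of hospital discharge, analyses will follow the intention-to-treat principle".
- **Other analysis set** (Analysis): a per-protocol comparison of program participants with usual care patients, both confined to those eligible at discharge.

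The article describes no analysis of all randomized patients.

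**The concern.** Randomization makes the two arms comparable at the moment of allocation. It gives no such assurance for a subset chosen later by events that allocation may influence. Here the subset is chosen at discharge, when one arm has had a navigator for part of the stay and everyone involved knows the assignment.

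The re-checked criteria differ in risk:

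- Age, distance of residence, place admitted from and an earlier referral are fixed before randomization. Re-applying them does no harm.
- Discharge to SNF or hospice and leaving against medical advice are decided after randomization. Contact with a navigator, or having the program available after discharge, could plausibly change them.
- Heart failure clinic attendance may belong with the second group, depending on what the criterion means.

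The patients removed are unlikely to be average. The Eligibility section itself describes SNF patients as at high risk of readmission. If one arm loses more such patients than the other, the remaining groups differ in baseline risk and the odds ratio shifts with no treatment effect. The confidence interval does not allow for this. The per-protocol analysis lies inside the same discharge-eligible set and would not reveal it.

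**Working it through.** **1. The plan's own figures.** Sample size section: 20% against 14%, 80% power, α = 0.05. The two-sided chi-square formula without continuity correction gives 615 per arm, 1230 in total, which matches the article. For 10% non-participation, 1230 / 0.9² = 1518.5, in line with the stated 1520. The reference effects are:

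- Design risk ratio: 0.14 / 0.20 = 0.70 (odds ratio 0.65).
- After 10% non-participation: 0.9 × 14% + 0.1 × 20% = 14.6%, and 14.6 / 20 = 0.73 (odds ratio 0.68).

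**2. Effect of exclusions when treatment does nothing.** Let every randomized patient have risk p = 0.20, let a fraction e be excluded at discharge, and let the excluded have risk r. The rate among those analyzed is

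(p − e·r) / (1 − e).

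The article gives no discharge-exclusion rate and no risk for the excluded, so e and r below are assumptions.

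| Control: e, r | Intervention: e, r | Control rate | Intervention rate | Risk ratio | Odds ratio |
|---|---|---|---|---|---|
| 10%, 30% | 10%, 30% | 18.9% | 18.9% | 1.00 | 1.00 |
| 10%, 30% | 15%, 30% | 0.170/0.90 = 18.9% | 0.155/0.85 = 18.2% | 0.97 | 0.96 |
| 10%, 35% | 15%, 35% | 0.165/0.90 = 18.3% | 0.1475/0.85 = 17.4% | 0.95 | 0.94 |
| 15%, 30% | 10%, 30% | 18.2% | 18.9% | 1.04 | 1.04 |
| 10%, 20% | 15%, 40% | 0.180/0.90 = 20.0% | 0.140/0.85 = 16.5% | 0.82 | 0.79 |

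The first row shows no bias when exclusions do not depend on arm. The fourth row shows that the bias can also run against the program.

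**3. Effect on the false-positive rate.** Assume 760 usual care patients analyzed at 20% risk after 10% were excluded. The intervention arm excludes a further d percentage points of patients with risk r, and there is no true effect. The nominal two-sided error is 5%.

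| d | r = 20% | r = 30% | r = 40% |
|---|---|---|---|
| 2 points | OR 1.00, 5.0% | OR 0.99, 5.1% | OR 0.97, 5.6% |
| 5 points | OR 1.00, 5.0% | OR 0.96, 5.9% | OR 0.93, 8.8% |
| 10 points | OR 1.00, 5.0% | OR 0.92, 9.1% | OR 0.85, 22.6% |

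A small imbalance hardly matters. A 10-point imbalance in high-risk patients does.

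**4. Price of analyzing everyone randomized.** If a further 10% of the intervention arm could not use the program, its rate becomes 0.9 × 14.6% + 0.1 × 20% = 15.14%. At 760 per arm, power for 20% against 15.14% is about 70%, compared with 79.5% for 20% against 14.6%.

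**The case against.** The best defense is that the restriction is prespecified, stated openly in the abstract, Eligibility and Analysis sections, applied by one rule to both arms, and explained. Patients stay in the arm they were randomized to. All of that is true, and it makes the set a reasonable one to report. It does not restore the randomized comparison, because an identical rule applied to something treatment can change may still remove different patients from each arm.

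Second, the full protocol and SAP are not shown and may contain a broader analysis or exclusion tables. This stands as a limit: one can say only that the article describes none. But the article's text places all analyses, and the primary comparison by name, on the discharge-eligible set. The point rests on that statement and not on silence.

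Third, some restriction is natural, since a patient who dies in hospital cannot be readmitted. This also stands. Under the Analysis section's rule that no recorded visit means no event, in-hospital deaths would count as not readmitted, so an all-randomized analysis needs its own rule for them.

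A reader might go further and infer that intervention patients use the program instead of the heart failure clinic and so stay in, while controls who attend it are dropped. The documents do not support this. The program is given in addition to usual care, and nothing says that one clinic replaces the other. The wording may mean a visit after discharge or an existing service status, since these patients are grouped with others who already have care management. Nor does the article say that the navigator's file decides eligibility: it records enrollment status and patients who decline.

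**Conclusion.** The point holds. The analysis called intention-to-treat is conditioned on events after randomization, some of which can depend on arm in an unblinded trial. The label is wrong, and the primary odds ratio is open to selection bias that neither its confidence interval nor the per-protocol analysis would show.

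The documents establish that bias is possible, not that it will occur or which way it would run. At an assumed 5-point imbalance and equal 30–35% risk among the excluded, the spurious risk ratio is about 0.97–0.95, small against the design value of 0.70 (0.73 after non-participation). It reaches 0.82 only if the excluded also differ sharply in risk between arms. All of these exclusion rates and risks are assumed. The matter still needs correcting before analysis, because it concerns the primary estimate and the correction is cheap.

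**What to change.** 1. Rename the discharge-eligible set modified intention-to-treat in the abstract and the Analysis section.
2. Run the same logistic model in all randomized patients and report it beside the modified set as the intention-to-treat result. State how in-hospital deaths are counted, for example by also showing the model in all patients discharged alive. Do not require both analyses to be significant: that would hold the trial to the power of the diluted analysis.
3. Determine discharge eligibility by one automated query, blind to arm, on fields recorded identically in both arms. This is a precaution, since the article does not say how the check is made.
4. For the heart failure clinic, use only status recorded before randomization.
5. Show discharge exclusions by arm and reason, so that readers can judge whether they differ.

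Cost: changes of wording and one more run of an existing model on outcomes that are already retrieved electronically. The drawback is dilution: power in the all-randomized set is about 70% at 760 per arm if a further 10% cannot use the program. That is the reason to report both sets rather than replace one with the other.
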